#### **4.3 Exclusion criteria**

A potential subject who meets any of the following criteria will be excluded from participation in this study:

##### *General criteria prior to randomization*

- Treatment with alitretinoin or azathioprine in the previous 3 months
- Hyperkeratotic palmar eczema as defined by the Danish Contact Dermatitis Group (6)
- Patients with predominantly atopic dermatitis, in which the hands are also involved. Patients with mild atopic dermatitis, in which the hands are mainly affected are eligible for inclusion.
- Psoriasis
- Active bacterial, fungal, or viral infection of the hands
- Pregnant/lactating or planning to become pregnant during the study period
- Treatment with systemic medication or UV radiation within the previous 4 weeks
- Mentally incompetent
- Immunocompromised status
- Known or suspected allergy to ingredients in the study medications
- Inclusion in a study of an investigational drug within 60 days prior to start of treatment
- Current malignancy (other than successfully treated non-metastatic cutaneous squamous cell or basal cell carcinoma and/or localized carcinoma in situ of the cervix)
- Current active pancreatitis
- Living vaccine (including bacillus Calmette-Guérin (BCG), varicella, measles, mumps, rubella, yellow fever, oral polio and oral typhoid) in the last 2 weeks or the planned application of such a vaccine during the study period
- Evidence of alcohol abuse or drug addiction
- Chronic or recurrent infectious diseases
- Contact sensitizations with clinical relevance to the hands, in which exposure to allergens is not avoided
- Hypervitaminosis A due to the use of vitamin A supplements containing >2000 IU

- Use of drugs with potential to change the effective dose of study drugs within the previous 2 weeks (see paragraph 5.2)

*Laboratory exclusion criteria post randomization*

- Alanine aminotransferase (ALAT) and/or aspartate aminotransferase (ASAT) values > 200% of the upper limit of normal
- Impaired renal function as indicated by a clinically relevant abnormal creatinine value (to be determined by investigator or treating physician)
- Anemia as indicated by a clinically relevant lowered hemoglobin value (to be determined by investigator or treating physician)

*Alitretinoin specific*

- Triglycerides > 200% of the upper limit of normal,
- Cholesterol or low density lipoprotein (LDL) cholesterol values > 200% of the upper limit of normal
- Uncontrolled hypothyroidism (to be determined by investigator or treating physician)

*Azathioprine specific*

- Patients with low or absent thiopurine methyltransferase (TPMT) activity (defined in our center as <52 nmol/gHb/hour, combined with genotyping showing homozygous or compound heterozygous mutations) and a subsequent risk for life-threatening myelotoxicity

#### **4.4 Sample size calculation**

This trial hypothesizes a superior response to azathioprine compared to alitretinoin in the treatment of severe chronic non-hyperkeratotic hand eczema.

A sample size of 52 in each group will have 80% power to be able to reject the null hypothesis of no difference between alitretinoin and azathioprine, using a chi-square test with a two-sided 0.05 significance level. In this calculation we used the following assumptions: randomization ratio is 1:1, and we expected the percentage of responders in the alitretinoin group to be 33% (10). Literature on the efficacy of azathioprine on hand eczema in terms of PGA is lacking. From a retrospective assessment of available patient data from our department, combined with clinical experience, we estimate 60% responders in the azathioprine group. We anticipate a drop-out of maximal 10% of randomized patients; a small percentage prior to first application of study drugs due to excluding laboratory measurements and a larger percentage during follow up, mainly due to subjective side effects. We therefore plan to include 116 patients in total, 58 in the alitretinoin group and 58 in the azathioprine group. (Calculated with the sample size

calculator of the Department of Biostatistics, Vanderbilt University, United States,  
available at <http://biostat.mc.vanderbilt.edu/wiki/Main/PowerSampleSize>.)

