## 1. INTRODUCTION AND RATIONALE

Hand eczema is a common skin disease of the hands. It can have far-reaching personal, psychological and occupational consequences that may have a drastic impact on the life of those affected. A point prevalence of 4% and a 1-year-period prevalence up to 10% in the general population in Sweden have been reported. (1) A Danish study in young adults showed an incidence of 8.8 per 1000 person-years, a point prevalence of 7.1% and a 1-year-period prevalence of 14.3%. Women are significantly more often affected than men. (2)

The clinical presentation of hand eczema varies widely, ranging from erythematous fissured skin to a vesicular eruption or palmar hyperkeratosis. The disease could also be approached etiologically, considering exogenous factors causing contact allergy (e.g. nickel, perfumes) and irritant contact dermatitis (e.g. water, soap) in addition to endogenous factors like atopic dermatitis. (3)

There is general consensus concerning the first line treatment of hand eczema in various guidelines. Emollients and topical corticosteroids are considered to be the mainstay of treatment in mild forms. If these fail, secondary options like phototherapy and systemic treatment are available. (3-6) A recent Cochrane review (unpublished), however, states that conclusions on the best way to treat hand eczema cannot be drawn from the wide diversity of studies that were carried out up until now. More head-to-head trials are needed. (7)

Alitretinoin is the only registered systemic treatment option for all clinical types of severe chronic hand eczema in the Netherlands. It is currently the most investigated drug in terms of patient numbers in the second line treatment of severe chronic hand eczema. In well-designed, pharmaceutical sponsored trials, 30 mg alitretinoin a day resulted in a clear or almost clear response in 48% of the participants, compared to 17% in placebo. In the hyperkeratotic subtype 54% responded, compared to 12% in the placebo group. In two non-hyperkeratotic subgroups (defined as pompholyx and fingertip in the study) only 33% of participants reached clearance or almost clearance, compared to 12-30% in the placebo group. (8-10)

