## 8. METHODS

### 8.1 Study parameters/endpoints

#### 8.1.1 Main study parameter/endpoint

##### *Severity of hand eczema*

The Physician Global Assessment (PGA) developed by Ruzicka et al, covers 5 degrees of severity (clear, almost clear, mild, moderate, severe) and takes into account the intensity and percentage of hand surface involved. (8,9) Response to treatment is defined as an improvement of  $\geq 2$  steps on the PGA. Severe hand eczema is defined as responding to treatment if a status of at least 'mild' is achieved. Moderate hand eczema is defined as responding to treatment if a status of at least 'almost clear' is achieved.

In this study the main endpoint is the between-group difference in response to treatment between baseline and 24 weeks of treatment.

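### The 33% alitretinoin planning rate counts only clear or almost clear hands, while the primary endpoint also counts severe-to-mild, so the 27-point difference and 80% power are not established for the endpoint to be tested

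*Protocol*

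**What the plan says.** Section 4.4 gives the planning basis: "A sample size of 52 in each group will have 80% power", "using a chi-square test with a two-sided 0.05 significance level", with equal allocation. For the comparator it says "we expected the percentage of responders in the alitretinoin group to be 33% (10", the number being the reference to the alitretinoin product information. For azathioprine it says "we estimate 60% responders in the azathioprine group", drawn from a retrospective look at departmental records and clinical experience. The same paragraph admits that there is no published azathioprine evidence in hand eczema expressed as PGA. Allowing for up to 10% drop-out, 58 per arm (116 in total) are to be randomised.

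Section 1, repeated in section 6.3, says what the 33% is. In two non-hyperkeratotic subgroups (pompholyx and fingertip) of the earlier alitretinoin trials, "only 33% of participants reached clearance or almost clearance, compared to 12-30% in the placebo group".

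Section 8.1.1 defines response in this trial as an improvement of at least 2 steps on a five-grade PGA (clear, almost clear, mild, moderate, severe). It then spells out the consequence: "Severe hand eczema is defined as responding to treatment if a status of at least 'mild' is achieved". For patients graded moderate, response means almost clear or better. The summary and section 10 use the same 2-step definition at 24 weeks. Section 4.2 admits patients with severe eczema.

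**The concern.** Section 4.4 calls both planning rates responders, but the 33% was counted under a stricter rule than the one this trial will apply. From severe, almost clear is 3 steps away and mild is 2. A severe patient who finishes at mild is a failure in the 33% and a success in this trial. Section 4.4 neither notes the difference nor adjusts for it.

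The azathioprine rate does not settle the matter, because neither section 1 nor section 4.4 says what counted as a response in the departmental data. The 27-point difference may therefore subtract a strict rate from a loose one, or it may compare two rates that are both off the trial's endpoint. At stake is the only stated justification for 116 patients in a superiority trial.

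**Working it through.** **Inputs.** All are from section 4.4 unless noted: two-sided 5% chi-square test, 1:1 allocation, 52 evaluable and 58 randomised per arm, p1 = 0.33 (alitretinoin), p2 = 0.60 (azathioprine). The response definitions come from sections 1, 6.3 and 8.1.1. The protocol gives no alitretinoin rate for a 2-step gain, so rates above 33% below are assumptions.

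**Step 1: reproduce the plan.** With p̄ = (p1 + p2)/2,

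n per arm = [1.96·√(2p̄(1−p̄)) + 0.842·√(p1(1−p1) + p2(1−p2))]² / (p2−p1)²

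Here p̄ = 0.465. The first root is 0.7054 and the second 0.6790, so n = 52.4. Power at n is

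Φ{[(p2−p1)·√n − 1.96·√(2p̄(1−p̄))] / √(p1(1−p1) + p2(1−p2))}

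At n = 52 this is Φ(0.831) = 79.7%. Drop-out: 52/0.9 = 57.8, rounded up to 58 per arm, 116 in total. The stated figures are reproduced, so the formula is not at fault.

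**Step 2: compare the two definitions by baseline grade.**

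| Baseline PGA | Clear or almost clear needs | Trial response needs | Same? |
|---|---|---|---|
| Severe | at least 3 steps | at least 2 steps (mild or better) | No |
| Moderate | at least 2 steps | at least 2 steps (almost clear or better) | Yes |

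From either grade, everyone who becomes clear or almost clear is also a 2-step responder. In the same patients:

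rate on the trial endpoint = 33% + share who start severe and end at mild.

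**Step 3: the 60% is already on the 2-step scale.** Only the alitretinoin rate moves. The assumed shares ending at mild are 5, 10 and 15 percentage points.

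| Alitretinoin v azathioprine | Power, 52 per arm | Power, 58 per arm |
|---|---|---|
| 33% v 60% (as planned) | 80% | 84% |
| 38% v 60% | 61% | 66% |
| 43% v 60% | 41% | 45% |
| 48% v 60% | 23% | 25% |

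**Step 4: the 60% is also on the stricter scale.** Both rates then move, by unknown amounts. If they rise equally, the 27-point gap is kept.

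| Alitretinoin v azathioprine | Power, 52 per arm |
|---|---|
| 38% v 65% | 79.5% |
| 43% v 70% | 80.2% |
| 48% v 75% | 81.7% |

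The protocol does not say which of steps 3 and 4 applies, nor that the rise would be equal in step 4.

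**The case against.** The best counter-argument is that power depends on both rates. A reader might infer that the 80% holds only if no alitretinoin patient stops at mild. Step 4 shows that this is wrong: if azathioprine gains as many patients at mild as alitretinoin does, power is essentially unchanged. The protocol does not support a firm statement that the trial is underpowered, and the figures of 61%, 41% and 23% depend on the 60% already being on the 2-step scale. This objection stands, and it limits the point to a power claim that is not established.

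A reader might also infer that this trial's alitretinoin rate must be at least 33%. That ordering holds only within the same patients. The 33% comes from two subgroups of other trials. This trial takes non-hyperkeratotic eczema at one tertiary centre, withdraws patients without PGA improvement at 12 weeks (section 8.4.1) and analyses by intention to treat (section 10). Its rate could differ from 33% in either direction for reasons unrelated to the definition. This also stands.

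Nor will every patient necessarily be severe at the baseline PGA. In the azathioprine arm eligibility is checked at week −5 and the PGA is scored at week 0 (Table 2), and section 8.1.1 has a rule for moderate baselines. For those patients the definitions coincide. This narrows the mismatch without removing it, since severe disease is the target population.

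Finally, intention to treat could put all 58 per arm in the analysis. Power under step 3 is then 66%, 45% and 25%, a modest gain that leaves the question open.

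**Conclusion.** The point holds as a mismatched planning input, not as an arithmetic error. By the protocol's own text, the comparator rate belongs to a stricter outcome than the primary endpoint, and the azathioprine rate has no stated definition. The 27-point difference and the 80% power are therefore not established for the endpoint that will be tested.

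The size of the effect on power cannot be fixed from the protocol. It ranges from none (both rates rise equally, about 80 to 82% at 52 per arm) to substantial: 61%, 41% or 23% at 52 per arm if the 60% is on the 2-step scale and 5, 10 or 15 points of alitretinoin patients end at mild. Those shares are assumptions; nothing in the protocol anchors them. Section 4.4 needs correcting because the trial's size rests on it.

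**What to change.** In section 4.4:

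- State the response definition behind the 33% and behind the 60%, including how response was judged in the departmental data.
- Re-express both rates as a PGA improvement of at least 2 steps at 24 weeks, giving the assumed share of severe patients who reach mild in each arm.
- Replace the single 80% claim with power at 52 and at 58 per arm over a range that covers both cases: only the alitretinoin rate rising, and both rates rising.

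Optionally, tabulate clear or almost clear at week 24 from the PGA already scored at that visit, so that the result can be set beside the figure used for planning. This helps interpretation but does not repair the sample size basis.

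The cost is protocol wording and a short power table, with no extra visits or assessments. The drawback is that the stated power may become less favourable; if so, the sponsor would have to justify 116 patients on the revised figures or reconsider the number.

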## **5. TREATMENT OF SUBJECTS**

### **5.1 Investigational product/treatment**

Group I will receive alitretinoin.

Group II will receive azathioprine.

Dosage, dosage modification and method of administration can be found in paragraph 6.6.

### **5.2 Use of co-intervention**

All patients will be given an emollient cream with instructions to apply it frequently. One week before the first intake of study drugs, concomitant treatment with a topical class II corticosteroid at maximum is permitted when needed, with a maximum application of one finger-tip-unit (FTU) for each hand daily. (17) This also applies for concomitant topical corticosteroid therapy during the study period. Higher class topical corticosteroids are not allowed as maintenance therapy.

Generally prohibited concomitant treatments during therapy comprise: systemic corticosteroids, other retinoids, any other systemic or topical anti-eczema therapy, phototherapy, immunosuppressive or cytostatic drugs.

Alitretinoin specific prohibited concomitant treatment: vitamin A supplements, tetracyclines and azole antimycotics. St John's wort should not be taken because of a possible interaction with hormonal anti-conceptive drugs. This could possibly result in a pregnancy, which is absolutely contraindicated because of the teratogenic nature of alitretinoin. (10)

Azathioprine specific prohibited concomitant treatment: allopurinol, febuxostat, ribavirin. Patients on cumarines are requested to inform their thrombosis service of treatment with azathioprine. Careful monitoring of coagulation is advised. (18)

### **5.3 Escape medication**

In case of an exacerbation or postponed treatment effect, patients are allowed to receive a maximum of 3 courses of rescue medication: mometasone furoate once daily for 1 week, with a maximum application of one FTU for each hand daily. (17)

## 6. INVESTIGATIONAL PRODUCT

The products of this study will be used as in usual clinical practice.

### 6.1 Name and description of investigational products

*Alitretinoin* is a retinoid drug. The pharmacological action of retinoid drugs may be explained by their effects on cell proliferation, cell differentiation, apoptosis, angiogenesis, keratinization, sebum secretion and immunomodulation. Unlike other retinoids, which are specific agonists of either RAR or RXR receptors, alitretinoin binds to members of both receptor families. The mechanism of action of alitretinoin in chronic hand eczema is unknown. It has been shown that alitretinoin has immunomodulatory and anti-inflammatory effects that are relevant to skin inflammation. CXCR3 ligands and CCL20 chemokines, that are brought to expression in eczematous skin lesions, are down-regulated by alitretinoin in cytokine stimulated keratinocytes and dermal endothelium cells. In addition, alitretinoin suppresses the expansion of cytokine activated leukocyte subsets and antigen presenting cells. It has been observed that in humans alitretinoin only minimally affects sebum secretion.(10)

*Azathioprine* is a prodrug of 6-mercaptopurine (6-MP). 6-MP is inactive in itself, but works as a purine antagonist. It requires uptake into the cell and intracellular anabolism to thioguanine-nucleotides (TGN's) for immunosuppression. The TGN's and other metabolites (e.g. 6-methylmercaptopurine nucleotides) inhibit *de novo* purinesynthesis and interconversions of purine nucleotides. The TGN's are also incorporated in nucleic acids and this contributes to the immunosuppressive action of the drug. Another potential mechanism of action for azathioprine comprises the inhibition of multiple pathways in nucleic acid biosynthesis. This impedes the initiation and accumulation of an immune response. Due to the nature of these mechanisms, azathioprine takes several weeks to months to show its therapeutic effect. (18)

### 6.2 Summary of findings from non-clinical studies

*Alitretinoin (from SPC text) (10)*

Acute toxicity

As with other retinoids, the acute toxicity of alitretinoin was low in mice and rats. The LD50 after intraperitoneal administration was >4000 mg/kg after 24 hours and 1400 mg/kg after 10 days. The approximate LD50 after oral administration in rats was 3000 mg/kg.

Chronic toxicity

Alitretinoin was tested in long-term studies up to 9 months in dogs and 6 months in rats. Signs of toxicity were dose-related and occurred at exposures similar to the human therapeutic exposure based on area-under-the-curve (AUC). Effects were characteristic for retinoids (consistent with hypervitaminosis A), and were generally spontaneously reversible.

#### Teratogenicity

Like other retinoids, alitretinoin has been shown to be teratogenic in vitro and in vivo. Due to the teratogenic potential of alitretinoin, women of childbearing potential must adhere to strict pregnancy prevention measures during and 1 month following alitretinoin therapy.

#### Fertility

Alitretinoin was tested in a study of fertility and early embryonic development in rats. No effects on male or female reproductive parameters were observed at the highest dose tested. However, systemic exposure in this study did not reach the level observed in patients.

As with other retinoids reversible effects on male reproductive organs were observed in experimental animals in the form of disturbed spermatogenesis and associated degenerative lesions of the testes. The safety margin in dogs with regard to the no-effect level of toxicity to male reproductive organs was 1-6 for a human dose of 30 mg.

#### Mutagenicity

In in vitro or in vivo tests, alitretinoin has been shown not to be mutagenic.

#### Carcinogenicity

Alitretinoin was tested in 2-year carcinogenicity studies in rats and mice. Dose-related retinoid-specific toxicity was seen at higher doses, but no carcinogenic potential was noted.

#### Phototoxicity

Alitretinoin was found to be phototoxic in vitro and in vivo

#### *Azathioprine (from SPC text) (18)*

Toxicological studies in animals have shown that the hematopoietic system is most strongly influenced by depression of mainly granulopoiesis and relative sparing of megakaryocytes and thus the formation of thrombocytes. In dogs azathioprine caused

death due to agranulocytosis. Related to the effect on hematopoiesis is the effect on the lymphatic system, with atrophy of the lymphatic tissue as was found in rhesus monkeys. Azathioprine, like 6-MP, can damage the liver. In dogs a reversible hepatotoxicity was noted. Dogs are very sensitive to this reaction.

Teratogenicity or embryoletality has been seen in a number of animal species with varying degree of susceptibility. In rabbits, a dose of 5-15 mg/kg body weight daily on days 6-14 of pregnancy produced skeletal abnormalities, in mice and rats, doses of 1-2 mg/kg body weight daily on days 3-12 were lethal to embryos.

Evidence of teratogenicity of azathioprine in man is equivocal. As with all cytotoxic chemotherapy, contraceptive precautions should be advised when either partner is receiving azathioprine.

Azathioprine was mutagenic in a number of in-vitro and in-vivo genotoxicity assays.

In long-term carcinogenicity studies of azathioprine in mice and rats, an increased incidence of lymphosarcomas (mice) and epithelial tumours and carcinomas (rats) were observed at dosages that were up to 2-fold the human therapeutic dosage.

### **6.3 Summary of findings from clinical studies**

#### *Alitretinoin*

In well-designed, pharmaceutical sponsored trials, 30 mg alitretinoin a day resulted in a clear or almost clear response in 48% of the participants, compared to 17% in placebo. In the hyperkeratotic subtype 54% responded, compared to 12% in the placebo group. In two non-hyperkeratotic subgroups (defined as pompholyx and fingertip in the study) only 33% of participants reached clearance or almost clearance, compared to 12-30% in the placebo group. (8-10) Retreatment of patients that previously had a response to alitretinoin treatment led to a second response to a new course of treatment in 80% of patients. Retreatment was well tolerated. (19)

#### *Azathioprine*

A few small studies have shown that azathioprine may have a beneficial effect on hand eczema. Scerri et al found a 75% good to excellent sustained clinical response in a case study in which pompholyx patients were treated with azathioprine. (12) In a case study by Pearce et al, 6 patients were treated with azathioprine for lymphoedema and hand dermatitis. 50% of patients reported a beneficial effect of the treatment. (13) In an Indian randomized comparative trial, conducted in 2013, chronic hand eczema patients were

treated with either topical clobetasol propionate 0,05% cream alone, or in combination with azathioprine. A 91% improvement of hand eczema severity index (HECSI) score at 24 weeks was found in the azathioprine group, compared to 39% in the control group. (14)

